  1. SECONDARY OBJECTIVES

1. To what extent can value of care variation in care be identified from ePROMs and ePREMs surveys?

- What is the share of suspected low-value care and suspected high-value care in Germany, per indication and in subgroups?
- How do ePROM and ePREM results differ according to age, gender, indication, city/state, healthcare system utilization (changes in frequency of outpatient practitioner attendance, prescriptions, hospitalizations, etc.), and DMP participation?
- Can ePROMs and ePREMs function as an early warning signal for deteriorating chronic conditions or adverse events such as hospital admission?

1. What are the benefits or drawbacks of PRO feedback (outcome reports) sent to patients?

- Are the PRO value reports understandable to patients?
- Can PRO feedback function as a positive nudge (lead to positive behavioral changes e.g., healthier or more active lifestyle, more active participation in medical treatment, actively approaching treating physicians in the office setting)?
- Are there any negative emotional reactions when receiving PRO feedback that shows values worse than those of a comparable group?

1. Background/Introduction

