   1. STUDY DESIGN

The study is an observational prospective cohort study with patients of four chronic disease areas with existing DMPs (asthma, chronic obstructive pulmonary disease (COPD), diabetes (type 1 and type 2) and coronary artery disease) with two sub-cohorts (DMP and non-DMP) for each disease.

- Type of control: none / group matched BARMER insurees (matching criteria: disease area, gender, age group)
- Level and method of blinding: none
- Method of treatment assignment: stratified randomized selection of study population
- Number of subjects: 200,000 patients invited (50,000 per chronic indication and about 25,000 in each sub-cohort)
- Duration of study: one year (four quarterly survey periods)

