  1. INTERVENTION

In addition to filling out the survey questions at four points in time (intervention 1), all participants will receive PRO feedback as a potential nudge (intervention 2). The PRO feedback will be a pdf report sent via email and available in their study participant profile, which graphically (line charts) shows the patients’ individual generic and disease-specific health status in comparison to the individual peer group. In addition to the visual feedback, the results will shortly be explained on the same page. The description will cover whether patient-individual PRO scores are better or worse compared to the peer group, and for longitudinal values, whether patient-related changes improved or worsened. Additional details on the scores, sub-scores, and calculations are shared with the patients on the following pages of the report. Peer groups are classified according to their disease, gender, and age group. The peer group is created based on individuals who have replied to the previous survey and will only be displayed if the group consists of at least four individuals. This threshold is set by the German General Data Protection Regulation. The report refers to the patients’ physicians as the main contact to discuss the results or in case of questions.

- 1. SAMPLE SIZE

The sample is drawn stratified randomly from insured patients of one large German statutory health insurance with about 9 million insured persons (of about 73 million statutorily insured persons in total in Germany) according to their diagnosis and/or disease management program status. A one-to-one matching of participants of one DMP with non-participants of a DMP but with the same proven diagnosis according to the ICD-10-GM system is made. Further stratification criteria are age group, gender, and health system utilization.

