As shown in Figure 1, the first point of contact will be a letter from the insurance to insured individuals with chronic diseases, who can then sign into the digital study via a QR code or link. For each of the different disease areas, a distinct care path is opened, with a sign-in process followed by selected PROMs and PREMs. The study covers a timeframe of one year with four overarching time intervals with dedicated questions. These are split into smaller tasks to facilitate the answering process for participants. The time intervals are split into smaller tasks to facilitate the answering process for participants. A few weeks after responding to the first set of questions (A & B), patients will receive a report with their individual PROM scores compared to a peer group, the PRO feedback (C). From the second interval onwards, patients will also receive the PRO feedback in a longitudinal visualization. Lastly, following the PRO feedback participants will be surveyed regarding their health behavior (D).

Figure 2 presents the questionnaires that will be used in the study per chronic disease group. PROM surveys include generic as well as disease-specific PROMs. The participants will receive individual reports on their patient-specific and peer group outcomes (PRO feedback) and will be asked about the comprehensibility of the report. Following the report, the participants receive a set of questions regarding the report’s comprehensibility and their health-related behavior.

[figure not shown]

*Figure 2: Survey items in the PROMchronic trial*

The primary data collected in this study is hence:

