**Patient reported indicators:**

- Generic PROM index score: PROMIS PROPr is a preference-based score which combines seven PROMIS domains of health status into one score (cognitive function, depression, fatigue, pain, physical function, sleep, social roles)
- Disease-specific PROM index scores for each chronic disease

Asthma: Asthma Impairment and Risk Questionnaire (AIRQ) score

COPD: Clinical COPD Questionnaire (CCQ) score

Diabetes: Problem Areas in Diabetes (PAID-5) score

Coronary artery disease: Seattle Angina Questionnaire (SAQ-7) score and Rose Dyspnea Scale (RDS) score

- PREM index score: Responsiveness of the health care system
- Looked at PRO feedback
- Comprehensibility of PRO feedback
- Helpfulness of PRO feedback
- Emotional reaction to PRO feedback
- Discussion of PRO feedback with physician(s)
- Health behavior in five dimensions:

Physical activity

Nutrition

Tobacco consumption

Alcohol consumption

Sleep duration

- Plans to change health behavior in the future
- Trigger for health behavioral change
- Overall health improvement
- Disease-specific health improvement

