- Using machine learning predictive models (long-short-term memory deep learning network for time trend classification, random forest, logistic regression, decision tree and/or support vector machine) to identify admission risk in Q3 and Q4 based on PROMs/PREMs in Q1 and Q2

*PRO feedback*

- Mainly: Statistically significant change in at least one of the health care behavior dimensions (see 4.2) and comparison of participants who opened the report vs. those who did not, using logistic regression (change/no change)
  - Physical activity: Shift of participants to a higher category
  - Nutrition: Shift of participants to “More healthy” from any other category
  - Tobacco: Shift of participants to a lower category
  - Alcohol: Shift of participants to a lower category
  - Sleep: Share of stable participants (no significant variation in sleep duration)
- Secondly: Descriptive exploratory analysis of the rates of the following two evaluation dimensions and statistically significant differences in subgroups (see 5.1 and 4.3):
  - Understandability
  - Helpfulness
  - Emotional change

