**Data analysis**

- Check for normality using the Shapiro–Wilk test
- Check for intraclass correlation using intraclass correlation coefficients
- Analyze missing data
- Descriptive statistics of patient and treatment characteristics
- Time series analysis
- Parametric and non-parametric methods
- Statistical tests depending on normality for the primary and secondary outcomes to compare:
  - Responders vs. non-responders (to the nudge)
  - DMP vs non-DMP members
- Linear and logistic regressions controlling for:
  - Significant patient characteristics
  - Significant other collected variables depending on the research question

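### The main nudge analysis compares self-selected openers and non-openers of the report, and choosing covariates by significance does not ensure that confounding by engagement is controlled

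*Protocol*

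**What the plan says.** Protocol Section 1.2 puts the question in causal terms: "Can PRO feedback function as a positive nudge", meaning whether it leads to positive changes in behaviour. Under Section 2.4, "all participants will receive PRO feedback as a potential nudge (intervention 2"). Section 2.1 calls the study an observational cohort and gives "Type of control: none / group matched BARMER insurees (matching criteria: disease area, gender, age group"). Its only mention of randomization is "Method of treatment assignment: stratified randomized selection of study population", which concerns who is sampled, not who gets feedback.

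In Section 5.2, under PRO feedback, the main analysis is a significant change in at least one behaviour dimension together with a "comparison of participants who opened the report vs. those who did not, using logistic regression (change/no change"). In Section 2.6 the exposure appears among the patient-reported items as "Looked at PRO feedback". The same section gives the order of events: PROM and PREM tasks A and B, then the report (C), and "following the PRO feedback participants will be surveyed regarding their health behavior (D").

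For adjustment, the Data analysis list in Section 5.2 plans linear and logistic regressions. The first group of covariates is "Significant patient characteristics". The second admits other variables that were collected, again if significant, according to the research question.

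**The concern.** Opening the report is a choice. People who are motivated, in a particular state of health or at ease with digital tools may be more likely both to open it and to change their behaviour. Openers would then show more change than non-openers even if the report did nothing. The stated adjustment rule selects covariates by significance, which is not a test of whether a variable confounds. A variable that strongly predicts opening but falls short of significance in whatever test is used would be left out. No measure of engagement and no earlier behaviour is named as a covariate.

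At stake is the main analysis of the third research question. An association produced by who chooses to read the report could be read as a benefit of sending it. The primary endpoint on participation and representativeness is not affected.

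**Working it through.** **Expected sample.** Section 2.5 gives 200,000 invited, about 30% responding, two-thirds allowing follow-up and about 40% of those completing all follow-up surveys: 200,000 × 0.30 × 2/3 × 0.40 = 16,000. This matches the stated figure.

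**Is another contrast free of self-selection?**
- Matched insurees (Section 2.1): the insurer data listed in Section 2.6 contain no measure of physical activity, nutrition, tobacco, alcohol or sleep, so they cannot supply the outcome.
- Change over time in the whole cohort: there is no concurrent group without feedback. Task D follows report C, so the text describes no behaviour measurement before the first report.
- Responders versus non-responders to the nudge (Section 5.2, Data analysis): also self-selected.

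**Size of the bias when feedback has no effect.** The protocol gives no opening rate and no rate of behaviour change, so every rate below is an assumption. Let half the participants be highly engaged. Let o1 and o0 be the opening rates, and c1 and c0 the change rates, in the engaged and the less engaged. Opening has no effect on change.

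- Share opening: O = 0.5·o1 + 0.5·o0
- Change among openers: p1 = (0.5·o1·c1 + 0.5·o0·c0) / O
- Change among non-openers: p0 = [0.5·(1−o1)·c1 + 0.5·(1−o0)·c0] / (1−O)
- Crude odds ratio: OR = [p1/(1−p1)] / [p0/(1−p0)]
- z = (p1−p0) / √[p(1−p)(1/n1 + 1/n0)], with p = 0.5·c1 + 0.5·c0, n1 = 16,000·O and n0 = 16,000·(1−O)

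Example with opening 90%/60% and change 25%/15%:
- O = 0.75, so n1 = 12,000 and n0 = 4,000.
- p1 = (0.1125 + 0.045)/0.75 = 0.210 and p0 = (0.0125 + 0.030)/0.25 = 0.170.
- OR = (0.21/0.79)/(0.17/0.83) = 1.30.
- z = 0.04/√[0.20·0.80·(1/12,000 + 1/4,000)] = 0.04/0.0073 = 5.5.

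| Opening, engaged/less | Change, engaged/less | Change, openers vs non-openers | Crude OR | z |
|---|---|---|---|---|
| 95%/50% | 30%/15% | 24.8% vs 16.4% | 1.69 | 11.4 |
| 90%/60% | 25%/15% | 21.0% vs 17.0% | 1.30 | 5.5 |
| 90%/60% | 25%/20% | 23.0% vs 21.0% | 1.12 | 2.6 |
| 80%/60% | 25%/20% | 22.9% vs 21.7% | 1.07 | 1.65 |
| 70%/60% | 22%/20% | 21.1% vs 20.9% | 1.01 | 0.3 |

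Section 5.1 sets two-sided 0.05, that is |z| above 1.96. The first three rows cross it and the last two do not. z scales with √N, so a quarter of the sample (4,000) halves it: 5.5 becomes 2.7 and 2.6 becomes 1.3.

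**The case against.** The strongest reply is that adjustment is planned and is wider than patient characteristics. A reader who stops at the first entry in the Section 5.2 list might infer that health before the report cannot be controlled. The document does not support that, because the second entry can bring in PROM and PREM scores and claims utilization. What remains is that entry depends on significance and that neither engagement nor earlier behaviour is named.

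Second, the magnitudes rest on assumed rates and are crude, whereas the planned models have covariates. The 16,000 are people expected to complete every survey, among whom engagement may vary less than an even high/low split implies. Both points stand. The table shows what is possible and does not predict a result.

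Third, the study is declared observational, the feedback is called only a potential nudge, the question is secondary, and no sentence says that the comparison proves causation. That is fair. The question in Section 1.2 is nonetheless causal, and this comparison is given as its main analysis. Section 2.6 also lists an item on what triggered a behaviour change. It helps interpretation, but it is the participant's own attribution and provides no comparison group.

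Fourth, covariate lists and propensity models are commonly left to a SAP, which is not shown. Their absence is therefore not the point. The point is a selection rule and a contrast that the protocol does state.

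**Conclusion.** The concern holds in a limited form. The main nudge analysis is a self-selected comparison, and the stated rule for choosing covariates does not ensure that confounding by engagement, health or earlier behaviour is removed. With no true effect, the assumed scenarios give crude odds ratios from 1.01 to 1.69. Moderate or strong confounding is significant at 16,000 participants, and weak confounding is not (OR 1.07, z 1.65).

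A reader might infer that the trial will report a benefit that does not exist. The documents do not support that: the rates are unknown, the planned adjustment may remove part of the bias, and weak confounding would leave little. Engagement differences may look like an effect of feedback, and the analysis as stated could not tell the two apart.

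**What to change.** In Section 5.2, replace selection by significance, for this analysis, with a fixed set of covariates measured before the report, used by regression or inverse-probability weighting:
- PROM and PREM scores from tasks A and B of the same period
- completion of earlier tasks
- claims utilization before the study
- age, gender, education, disease and DMP status
- behaviour at the previous task D

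Relate opening of report t to the change in behaviour from task D at t−1 to task D at t, from the second period on. A window from t to t+1 would not serve: behaviour at t is already measured after report t, and the window also contains report t+1. Use the Section 3 population and not only full completers, among whom completion of earlier tasks would hardly vary.

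State the result as an association, not as evidence that feedback caused the change.

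The cost is analysis wording and one model, using data that are largely already planned. Completion can be derived from the responder segments in Section 4.2. The claim becomes weaker, the first report drops out of the change analysis, and unmeasured motivation may still confound the result.

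### The main PRO-feedback analysis counts only favourable behaviour shifts for four of five behaviours, so worsening after the report is never counted or tested

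*Protocol*

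**What the plan says.** Section 5.2 of the Protocol, under Secondary Outcomes, PRO feedback, gives the main analysis of the third research question. It looks for "Statistically significant change in at least one of the health care behavior dimensions", with a "comparison of participants who opened the report vs. those who did not, using logistic regression (change/no change"). It then lists what counts for each behaviour:

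- For exercise, only an increase is named: "Physical activity: Shift of participants to a higher category"
- For diet, only arrival at the favourable answer is named: "Shift of participants to “More healthy” from any other category"
- For smoking, and in the same terms for drinking, only a reduction is named: "Tobacco: Shift of participants to a lower category"
- For sleep, what is counted is how many people stay stable.

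The first four behaviours name one direction, the favourable one. The fifth counts absence of change. Neither section 5.2 nor the outcome list in section 4.2 gives a category, count or test for behaviour that gets worse.

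The objective in section 1.2 asks: "What are the benefits or drawbacks of PRO feedback (outcome reports) sent to patients". Section 4.2 lists the impact of feedback on behaviour, overall and per subdimension, without a direction. Section 5.1 makes tests two-sided.

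**The concern.** With a two-level outcome and these definitions, a participant who becomes less active, or smokes or drinks more, has only one place to go: the same level as someone who did not change. The Protocol does not write this coding out. It is an inference, but no other coding fits the listed definitions.

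The odds ratio for openers against non-openers then depends only on how many people improved. Two-sided testing does not help, because the two sides are more improvement and less improvement; worsening is on neither. Movement in both directions is conceivable from the study's own design. Section 2.4 has the report tell each patient whether their scores are better or worse than those of peers, and these two messages need not push behaviour the same way. If the report raises both improvement and worsening, the planned analysis shows the first and hides the second, and the conclusion on the nudge would be wrong or incomplete.

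**Working it through.** **Inputs from the Protocol.** Section 2.5 gives 200,000 invited, about 30% responding, two-thirds of these allowing follow-up, and 40% of those completing all surveys: 200,000 × 0.30 × 2/3 × 0.40 = 16,000. This reproduces the stated 16,000. The Protocol gives no shift rates, opening share or effect size for behaviour, so every rate below is an assumption.

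**Step 1: harm exceeds help.** Assume 12,000 openers and 4,000 non-openers, with openers 20% better and 25% worse, non-openers 15% better and 15% worse.

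- Planned odds ratio: (0.20/0.80)/(0.15/0.85) = 1.42.
- SE of the log odds ratio: √(1/2,400 + 1/9,600 + 1/600 + 1/3,400) = 0.050. z = ln(1.417)/0.0498 = 7.0, in favour of the report.
- Odds ratio for worsening, not planned: (0.25/0.75)/(0.15/0.85) = 1.89.
- Net shift: 20 − 25 = −5 points in openers, 15 − 15 = 0 in non-openers.
- SE of the difference in net shift: √[(0.45 − 0.05²)/12,000 + 0.30/4,000] = 0.0106. The difference is −5 points, 95% CI about −7.1 to −2.9.

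The same data support a strong benefit under the planned coding and a clear net loss once worsening is counted.

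**Step 2: smaller, balanced movement.** Assume 10% better and 10% worse in non-openers, 12% and 12% in openers, and 70% opening (11,200 against 4,800).

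- Planned odds ratio: (0.12/0.88)/(0.10/0.90) = 1.23.
- In 20,000 simulated studies, favourable-only coding gave a significant benefit in about 96%. A net score (+1, 0, −1) was significant in 4.8%, the nominal level.
- If openers are instead 12% better and 14% worse, the planned odds ratio is still 1.23. The odds ratio for worsening is (0.14/0.86)/(0.10/0.90) = 1.47 and is not seen.

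**Step 3: random re-reporting alone.** Let each of four independent behaviours show a chance favourable shift with probability u. The share with at least one is 1 − (1 − u)⁴: 18.5% at u = 5%, 34.4% at 10%, 47.8% at 15%, 59.0% at 20%. When u = 10% in both groups, the simulated type I error of the opener contrast is 4.8%. Equal noise raises the raw share but creates no false difference.

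**Step 4: sleep.** If stable sleep also satisfies the at-least-one rule, and 50% to 90% are stable (assumed), the share at u = 10% is 1 − 0.9⁴ × (1 − s): 67% at s = 0.5 and 93% at s = 0.9. A stability item inside a change composite would then dominate it.

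**The case against.** The best defence is that the outcome fits the question asked. Section 1.2 breaks its benefit-and-drawback question into parts. The behaviour part asks whether feedback acts as a positive nudge, and the drawback part concerns emotional reactions, which section 5.2 covers separately. An improved/not-improved outcome is a legitimate answer to the nudge question. That stands, and it is why the improvement model should stay. It does not make the answer complete: section 4.2 states the behaviour impact without a direction, and a nudge that worsens as many people as it improves is not a positive one in any useful sense.

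It can also be said that coding details belong in a statistical analysis plan, which is not at hand and might tabulate worsening. That is fair as to the 1/0 rule, but the Protocol itself fixes the direction item by item.

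A reader might go further and infer that random fluctuation in self-report will by itself make the report look beneficial. The documents do not support this. The contrast is opened against not opened, and noise of equal size cancels. It would matter only if openers' answers varied more, which nothing in the Protocol shows, or if the raw favourable share were read without a comparison. Nor is it right that all five behaviours count only favourable shifts; sleep does not.

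Finally, replacing the binary outcome with an ordinal odds ratio or a net shift alone can also hide an effect that pushes people both ways, since the two movements offset. This stands and shapes the remedy.

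**Conclusion.** The point holds in a limited form. As written, the main PRO-feedback analysis can show improvement in activity, nutrition, tobacco and alcohol but cannot show worsening. Whenever the report raises the improving share, the odds ratio exceeds 1, whatever happens to the worsening share. In the illustrations the planned odds ratio was 1.42 with a net change 5 points worse in openers, and 1.23 with a net effect of zero. These sizes rest on assumed shift rates and opening shares; only the 16,000 comes from the Protocol. The Protocol gives no evidence that feedback does move people both ways, so this is a gap in what can be concluded, not a demonstrated bias. It concerns the main analysis of the third research question, not the primary endpoint, and is worth correcting before analysis.

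**What to change.** In section 5.2, classify activity, nutrition, tobacco and alcohol each as better, same or worse. Keep the planned improvement model. Add the same opener against non-opener logistic model with worsening as the outcome. For each behaviour, report the shares better and worse in both groups, and the net shift (better minus worse) with its confidence interval. State that a positive nudge will be concluded only when the improvement is not matched by worsening. Keep sleep out of the favourable-shift composite, or define it in the same three levels.

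The data and covariates are unchanged. The cost is one extra model per behaviour and slightly longer reporting.

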   1. GENERAL METHODOLOGY

Quantitative variables will be described as mean (respectively median), standard deviation (inter-quartile range), number, and rate of missing data, and compared between arms with a t-test, or if not appropriate with a Wilcoxon rank-sum test. Qualitative variables will be reported as absolute and relative frequencies, number, and rate of missing variables, and compared between sub-cohorts with the Chi-square test or the Fisher’s exact test. Variables will be compared between both sub-cohorts (DMP and non-DMP participants). P-value <0,05 with a bilateral hypothesis will be considered significant. All the analyses will be carried out using R, SAS, and other statistical software for Windows.

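### The main PRO-feedback analysis is framed as behaviour change but counts unchanged sleep as meeting the criterion, and its any-one-dimension success rule is faulty on either reading

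*Protocol*

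**What the plan says.** Protocol section 5.2, under Secondary Outcomes, PRO feedback, gives the main criterion as "Statistically significant change in at least one of the health care behavior dimensions", together with a "comparison of participants who opened the report vs. those who did not, using logistic regression (change/no change"). Section 2.6 lists "Health behavior in five dimensions": physical activity, nutrition, tobacco, alcohol and sleep duration.

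Section 5.2 then defines the counted event for each. For four dimensions it is a favourable move, for example "Physical activity: Shift of participants to a higher category". For the fifth it is "Sleep: Share of stable participants (no significant variation in sleep duration").

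Section 5.1 sets the general threshold: "P-value <0,05 with a bilateral hypothesis will be considered significant". The protocol states no adjustment for testing several dimensions.

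On timing, section 2.6 says: "A few weeks after responding to the first set of questions (A & B), patients will receive a report with their individual PROM scores", and then: "Lastly, following the PRO feedback participants will be surveyed regarding their health behavior (D"). The protocol does not say which measurement a shift is counted from. Section 2.4 says that every participant is sent the report.

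**The concern.** The outcome is called change, yet for one of its five components staying the same is the event that counts. The third research question asks whether feedback moves patients towards healthier behaviour, and this is the main analysis meant to answer it. An outcome met by people who altered nothing, and missed by people whose only change was better sleep, does not measure that.

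The rule that any one dimension suffices is fixed in the protocol without saying whether it means five tests or one composite per participant. The first reading raises the chance of a spurious claim of effect. The second lets the sleep item hide a real difference.

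The described order of report and survey also raises the question of whether behaviour is recorded at all before the first report.

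**Working it through.** **Plan's own figures.** The protocol gives no power, effect size or family-wise error rate for this analysis. Its only computed figure is the expected number of complete data sets (section 2.5), which reproduces: 200,000 × 0.30 × 2/3 × 0.40 = 16,000.

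**Step 1: the criteria side by side.**

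| Dimension | Event that counts |
| --- | --- |
| Physical activity | move up |
| Nutrition | move to the healthier category |
| Tobacco | move down |
| Alcohol | move down |
| Sleep | no move |

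Sleep is opposite in kind to the other four.

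**Step 2: reading A, five tests, any one suffices.** Inputs: five dimensions (section 2.6), two-sided 0.05 each (section 5.1), no adjustment.

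- Independent tests: 1 − 0.95^5 = 0.226.
- Upper bound under any dependence: 5 × 0.05 = 0.25.
- Equal pairwise correlation of the test statistics (simulation, 1,000,000 draws): 21.8% at 0.2, 20.9% at 0.3, 18.2% at 0.5, 12.7% at 0.8.
- Dropping sleep alone does not cure this: 1 − 0.95^4 = 0.185.

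These figures count a significant difference in either direction. Counting only differences that favour openers, the independent figure is 1 − 0.975^5 = 0.119.

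**Step 3: reading B, one composite per participant.** Let s be the share with stable sleep and q the chance of a favourable shift in each other dimension. With independent dimensions, and stable sleep unrelated to opening the report, the share counted as changed is 1 − (1 − s)(1 − q)^4. The protocol gives neither s nor q, so all values below are assumptions.

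- Nobody changes anything (q = 0): the share counted as changed equals s. With s = 50%, 70% or 90%, that share of participants meets the criterion.
- q = 0.10 for non-openers, 0.15 for openers, sleep left out: 1 − 0.90^4 = 0.344 and 1 − 0.85^4 = 0.478. Odds ratio = (0.478/0.522)/(0.344/0.656) = 1.75.
- Same q, sleep included, s = 0.80: 1 − 0.20 × 0.656 = 0.869 and 1 − 0.20 × 0.522 = 0.896. Odds ratio, from unrounded values = 1.30. The difference shrinks from 13.4 to 2.7 percentage points.
- s from 0.60 to 0.90: odds ratio 1.35 to 1.27.

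**Step 4: timing.** Section 2.6 gives the order within an interval as question sets A and B, then report C, then behaviour survey D. A second sentence in that section again puts the behaviour questions after the report. The text describes no behaviour item before the first report. If there is none, the first D value of someone who opened the first report already contains any immediate response to it.

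**The case against.** The strongest reply is that this is a secondary outcome in an observational cohort. Multiplicity for such outcomes is commonly settled in a statistical analysis plan, which is not at hand, and section 5.1 gives only a general threshold. That limits the weight of the point. It does not remove it, because the protocol itself fixes the rule that any one dimension suffices, and the sleep criterion contradicts the outcome it belongs to whatever a later plan adds.

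Several stronger readings are tempting and are not supported:

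- *That the analysis suffers both inflated error and dilution.* The two are alternatives. Five separate tests leave the other four dimensions untouched by sleep; one composite is one test.
- *That the baseline certainly follows the first report.* The order in section 2.6 supports this, but it is an inference. Figures 1 and 2, which show tasks and survey items, are not visible here, and the text does not say that behaviour is asked only in D.
- *That the analysis cannot show any behaviour change linked to the report, or that it misses the largest nudge.* Reports continue after the first interval, so shifts between later D surveys remain observable. Participants who did not open the first report have a first D value unexposed to its content. Nothing in the protocol says that the first report has the largest effect.
- *That people already in the best category are wrongly scored as unchanged.* The protocol does not say how they are handled; defining who can shift may be left to the analysis plan.

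The dilution figures rest on assumed inputs. What stands without them is the direction: under the Step 3 assumptions, adding the sleep item pulls the contrast towards no difference.

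**Conclusion.** The point holds for the sleep criterion and the success rule. Sleep stability is counted as an event within a change outcome, which is a contradiction in the protocol's own list and needs no assumption.

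The success rule is badly fixed on either reading. As five tests, the chance of at least one false positive is 22.6% under independence, about 13% to 22% at correlations of 0.8 to 0.2, and never above 25%. As one composite, the error rate is not inflated, but under the assumed inputs the odds ratio falls from 1.75 to 1.30 (1.35 to 1.27 for 60% to 90% stable sleepers).

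The baseline point is conditional on what Figures 1 and 2 show. If no behaviour item precedes the first report, what is lost is that report's immediate effect among those who opened it.

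This should be corrected. It concerns the answer to the third research question and leaves the primary endpoint untouched.

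**What to change.** 1. Take sleep out of the change outcome and analyse change in sleep duration separately. Cost: wording.
2. State one success rule. Either make a composite of the other four dimensions the single main test at 0.05, or test the dimensions separately with Holm. Over four dimensions, the smallest p-value is then compared with 0.05/4 = 0.0125. If a sleep result may also count as success, include it in the family, and the first threshold is 0.05/5 = 0.01. Cost: wording.
3. Name the measurement from which a shift is counted. If no behaviour item precedes the first report, ask the same items in task A or B of the first period and use them as baseline. Cost: a few minutes of survey time, once. If that is no longer possible, limit the claim to changes after the first D survey, and state that an immediate effect of the first report among its openers is not captured.
4. Report the comparison of openers with non-openers as an association. Everyone is sent the report and participants choose whether to open it; steps 1 to 3 do not remove that self-selection. Cost: wording.
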